**Protocol Synopsis**

The rapid TB diagnosis is essential for decreasing the TB transmission and so the number of TB infected individuals. The bacilloscopy has low sensitivity and the major problem of the culture for mycobacteria is the long time of results realeasing. In spite of the costs, new tests can reinforce the Hospital Program of TB Control. The studies on MGIT accuracy have showed similar results with those obtained with the gold standard – culture on solid medium – as on the *M.tuberculosis* isolation as on susceptibility test to major drug for TB treatment. Using a pragmatic clinical trial design this study intends to evaluate the effectiveness of MGIT test versus routine culture methods in two university hospitals.

**Eligible Patients**

Individuals aged 16 or more, assisted in university hospital and secondary health unit in Rio de Janeiro, Brazil, under tuberculosis suspicion (TB), with or without anti-TB treatment in the past.

**Excluded patients**

Individuals that do not sign the Term of Free and Clear Consent (or their legal representative) or when there is a refusal of participation. Patients with known active TB

**Study Planning:** Pragmatic, open and randomized clinical trial to be accomplished in two university hospitals in the southeast area of Brazil.

**Intervention**

After the randomization, TB suspects will be submitted to MGIT or culture in solid Löwenstein-Jensen medium (gold standard)

**Main objective:**

1. The primary outcome was defined as the proportion of patients in each group whose initial prescription changed by the second month after randomization. The ‘change’ could be initiating or stopping TB treatment.

**1) RATIONALE**

The rapid diagnosis of TB is important in order to prevent the disease. However, little progress has been done in the last 50 years. New techniques such as the amplification of nucleic acids and automated systems using culture in liquid medium are very expensive and depend on sophisticated techniques that make them inadequate for routine use in "low income countries." Yet, even in "middle income countries" as in Brazil, where such technologies could be used in the public system and TB is endemic, the TB diagnosis has been based only on clinical suspicion, chest radiography and bacilloscopy exam (BAAR) of the sputum. Despite the low sensitivity (40% to 60%) of the sputum bacilloscopy, it is still one of the most important tests for the TB diagnosis, as it detects the patients that present a higher chance of infecting the community. Besides, in the developing countries a low incidence of the non tuberculosis mycobacterium (NTM) disease is observed. In these areas, the sputum bacilloscopy has a highly positive predictive value. However, in most of these countries, in practice, the culture for mycobacteria, whose sensitivity is higher (80% to 85%) than the bacilloscopy in the diagnosis of the lung TB, is carried out in solid medium, Löewenstein-Jensen (LJ), and is only performed in selected clinical cases (cases of treatment failure, patients with negative bacilloscopy). The major problem of the LJ culture is its long time of incubation (4 to 6 weeks) and the sensitivity test is accomplished from the culture and not from the clinical specimen, which demands several additional weeks for the obtainment of the results. In practice, in these countries, with the universal use solely of the sputum bacilloscopy, about 30% to 40% of the patients assisted in Primary Health Units in developing countries such as Brazil are treated of TB without bacteriological confirmation.

Brazil has the second largest number of TB cases in Latin America, with approximately 92.000 yearly new cases and the thirteenth largest number of cases in the world. The largest incidence rate of drug resistant TB (DR- TB) and of TB associated to HIV (TB-HIV) occurs in the metropolitan areas of Vitoria, Rio de Janeiro and Porto Alegre. The analysis of the preliminary data described in the national literature, the primary multi-resistant TB rate (MDR-TB) varies from 1 to 3% in the Primary Health Units (UPS) and from 5 to 12% in the Hospital Units, being higher among HIV+ patients. The highest TB lethality rate occurs due to the incorrect diagnosis accomplished in Hospital Units, Emergency Units, usually without TB control activities. In these hospitals, only 30% of the bacteriology laboratories perform culture tests for mycobacterium and they seldom make available the result of the TB bacillus sensitivity test to drugs. It is considered that in 20% to 30% of these cases the TB diagnosis was incorrect and the inadequate treatment probability is still higher in areas or in Health Units with a more extensive assistance to HIV infected patients or co-morbidity bearers, as in Hospital Units.

In 2004, it was emphasized in the Guidelines of National Norms/Policies of the Ministry of Health the need to introduce the method of culture for mycobacterium in an universal way in areas with high HIV infection rate and sensitivity to drugs tests (TSD) in reference Health Services or that presented high prevalence of DR-TB, as in hospitals, prisons, etc.

With the aim of stopping the global increase of TB, the WHO has recommended the DOTS strategy since 1993. This strategy is based on the diagnosis of pulmonary TB through sputum bacilloscopy and the shortened treatment schedule containing rifampicin (RIF), isoniazid (INH), pyrazinamide (PZA) and ethambutol (EMB). Yet, even with the DOTS strategy adoption in the areas or in Health Units where the MDR-TB is highly prevalent, the use of the first line schedule treatment (INH, RIF, PZA and EMB) is not effective and is contributing to the increase of primary MDR-TB in several areas of the world. In Russia, MDR-TB was initially prevalent only in patients with TB in the prisons, but recently, in these areas, the primary MDR-TB is occurring in patients assisted in Hospital Units or in Primary Health Units (UPS). Studies with mathematical models show that 75% of the MDR-TB cases need to be detected and 80% of them must present a favourable result so that the incidence of new MDR-TB cases is reduced in these areas. With the MDR-TB treatment, even with standardized schedules as the ones available in Brazil, only 60% to 70% of the patients obtain favourable results with the treatment. The rapid diagnosis of almost all of the MDR-TB cases has, therefore, become essential for the success of the program in these places.

The *M*. *tuberculosis* sensitivity to drugs determination consists basically in modifications of the minimum inhibiting concentration method in solid medium culture (proportions, resistance reason and absolute concentrations) and in liquid medium culture (BACTEC 460TB)*.* The methods carried out in solid medium culture, although quite reproducible, are very arduous, need great biosafety strictness and their results are given after a long period of time (15 to 30 days). The method validated in the Bactec 460TB system (liquid medium culture), in spite of being operationally simple and providing a rapid result, is a method whose radiometric principle drastically restricts its use. Besides those aspects, it has to be mentioned that the identification of the *M. tuberculosis* compound*,* obtained by phenotypic or genetic analyses, is a mandatory prerequisite for the accomplishment of the drug sensitivity test*.* The existent identification tests are fully reliable and of low cost. Nevertheless, they do not provide a swift result. In these situations, the MDR-TB bearer patients (mainly those in hospitals, infected by HIV and/or co-morbidity bearers) have frequently used the inappropriate schedule and/or developed to death before medical measures were taken.

In the last years, in the United States of America (USA), the *Center for Disease Control* (CDC) has recommended the use of the MGIT system (Mycobacteria Growth Indicator Tube) developed by the same company that developed the BACTEC 460 TB system (Becton Dickinson Diagnostic Instruments Systems, Sparks, Md). That is a non-radiometric method that contains the Middlebrook 7H9 modified liquid medium and is based on the same principle of the MGIT system, but is a totally automated system that presents continuous monitoring equipment, capable of 960 simultaneous tests. The instruments collect the fluorescence data of each tube at every 60 minutes and when an increase of this fluorescence is detected, the instruments indicate the tube as positive.

The development of new products for the tuberculosis diagnosis faces some challenges, the same way it is observed in the development of new medicines for neglected diseases: scarce financial resources and the market logic that reduces considerably the interests of large companies, since the use of the final product will be almost totally accomplished by the government of the different countries, usually not fulfilling their contracts, exactly where such diseases are prevalent.

In the last years, it has been emphasized the necessity of the accomplishment of Phase IV clinical trials, called pragmatic, which assess interventions in the nearest possible way to the real conditions in which they are applied in the clinical practice, serving as a support for taking decisions, in opposition to the so called explanatory Phase I, II, III clinical trials, carried out in more controlled conditions, answering questions about if and how does an intervention work; these questions are necessary to obtain the registration and commercialization of products.

Pragmatic studies, for being developed in routine conditions, do not complicate the usual practice and for this reason they are cheap and get the voluntary collaboration of the team.

The attainment of such studies does not raise great interest from the industries and unfortunately their execution usually is not considered a priority on the part of the governments be it at federal, state or municipal level or by the public policies formulators.

Studies already accomplished have shown that the BACTEC MGIT 960 performance is equalled to the BACTEC 460 one, with the advantage of being a non-radiometric method, supplying results in less time than the LJ solid medium. Recently, the Food and Drug Administration (FDA) has approved the automated method that uses the liquid medium called BACTEC MGIT (Mycobacteria Growth Indicator Tube) 960 that besides being as non-radiometric as the previous version (BACTEC460), provides a reliable TB and DST diagnostic result in less time than the LJ solid medium (10 to 15 days).

Usually, when the diagnostic kits are validated by the US FDA or by the European regulatory organizations, the regulatory organizations of developing countries tend to provide the registration for commercialization. In the last years, though, in Brazil, researchers of the Brazilian Net of TB Research (REDE-TB) have suggested that before releasing the registration and its allocation in the national market, the new diagnostic methods, mainly the ones related to the public health impact diseases should be submitted to an evaluation of their effectiveness and cost-effectiveness relation, in routine conditions, through pragmatic clinical trials.

Since there is no report in the literature of studies about pragmatic clinical trials and the cost-effectiveness of new technologies for the drug sensitive tuberculosis (DS-TB) and DR-TB diagnosis in Hospital Units of emerging countries, the Becton and Dickinson Company sought the REDE-TB in 2002 and proposed a partnership in this area. Recently, a Bactec MGIT 960 inter-laboratorial validation study has been concluded in reference laboratories in the cities of Rio de Janeiro, São Paulo and Vitória, with excellent results (Giampaglia et al, Multicentre evaluation of automated BACTEC 960 system for susceptibility testing of Mycobacterium tuberculosis. [Int J Tuberc Lung Dis](javascript:AL_get(this,%20'jour',%20'Int%20J%20Tuberc%20Lung%20Dis.');). 2007; 11: 986-991). Following a strategic planning, there has been agreed on the accomplishment of a study on phase III/IV of this technique in hospital or Primary Health Units with different TB/HIV rates. The company took the responsibility in supplying the inputs. In the present project, the evaluation of the clinical impact and cost-effectiveness relation of a new TB diagnostic technique is intended. This will take place in the same Health Units in which the Diagnostic Clinical Trials (accuracy analysis in routine conditions) are being carried out by REDE-TB researchers.

**2.- Hypothesis.** The use of a new technology (BD960) for the TB, MDR/TB investigation in secondary health and hospital units, besides reducing the intra-hospital TB transmission and the cost of the hospitalized patient's treatment, will also greatly reduce the morbid/lethality of TB patients, as they are usually bearers of other co-morbidities, mainly the HIV infection or the ones that use immunosuppressant chemotherapy. With the use of the current diagnostic investigation routine in the participating health units (method of proportions), the drug resistance diagnosis is usually available too late, when adverse effects and/or death have already occurred.

3. - **METHODOLOGY DETAILING**

**3.1 - Location of the Study**

1. Hospital Complex: Clementino Fraga Filho University Hospital and Chest Diseases Institute of the Federal University of Rio de Janeiro (HUCFF-IDT/UFRJ), located in the city of Rio de Janeiro.

2. Policlínica Augusto Amaral Peixoto (PAAP) – Municipality Health Secretary - Rio de Janeiro, Brazil.

**3.2 - Selection of Patients / Ethical Aspects**

Patients will be considered eligible in the participating health units with TB suspicion. Written consent will be obtained from all participants. The verbal consent with the signature of a witness will be obtained for individuals unable to read. The individuals will be informed that the study is being brought about to determine the effectiveness of a new diagnostic test for TB. For the candidates that choose not to be included in the trial, the standard diagnostic investigation will be offered, characterizing them as not participants of the study. The consent process will include the information provision regarding the risks and benefits of the drugs of the study.

**3.3 Inclusion Criteria**

a) age > 16 years; b) with clinical and suggestive laboratorial data of the first episode or active TB;

**3.4. Exclusion Criterion**

a) Patients that do not sign the Term of Free and Clear Consent (or his/her legal representative) or refuse to participate; b) Patients under anti-TB treatment; c) history of culture positive for M tuberculosis in the last 6 months prior of randomization.

**3.5. Interventions**

After randomization, clinical specimens from TB suspects will be submitted to MGIT or culture in Löwenstein Jensen solid medium (gold standard) at the HUCCF-UFRJ Mycobacteriological Laboratory. The accomplishment of such tests does not incur in risk for the patient.

**3.5.1. Description of the tests**

Respiratory and non-respiratory specimens, naturally contaminated, will be collected in disposable receptacle. The specimens should be given to the laboratory up to 24 hours after being collected and will be submitted to bacilloscopy after the Ziehl-Neelsen coloration. After being processed by the Kubica method, they will be cultivated by the BACTEC MGIT 960 method and in Löwenstein-Jensen in Rio de Janeiro and in Vitoria, and by the BACTEC MGIT 960 method. Cultures contaminated by other microorganisms will be called as contaminated and considered as negative for calculation in statistical tests. In the clinical specimens of the included patients, the sensitivity test will be carried out by the gold pattern tests and by BACTEC MGIT 960. Additionally, the positive cultures will be appraised as for the sensitivity of *M. tuberculosis* for isoniazid, rifampicin, streptomycin and ethambutol by the indirect test of proportions (one strain/patient).

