**3.6. Randomization - Clinical procedures for Open Clinical Trial Practice**

The physician that routinely evaluates the patients under active TB suspicion, invited to voluntarily participate of the study, once deciding the patient's inclusion in the protocol will request an envelope that contains in its external side four key questions: a) which is the patient's probability to present TB (high/intermediary or low); b) the choice above was based in the results of radiological examination; c) in his/her opinion, should the patient begin anti-TB treatment (yes or not) d) what is the patient's risk of having resistant TB (high/intermediary or low). The four questions filled out, the doctor will open the envelope and inside it he/she will identify which is the diagnostic method that should be requested for the patient. The envelopes will be numbered in growing order and the indication of the diagnostic tests inside them has been previously randomized by a professional non-participant of the study. This procedure **attempts to guarantee the concealing of the randomization and at the same time it will be possible to check the success of the randomization**.

In the routine investigation of patients under TB suspicion, the following information is collected in standardized forms: a) socio-demographic data; b) organs and human body systems examination; c) exposure to TB, disease and treatment history; d) past pathological history; e) physical exam; f) chest X-ray result; g) tuberculin skin test result; h) HIV test result.

Respiratory specimens include spontaneous sputum, induced sputum and bronchoalveolar wash. Non-respiratory specimens include biopsy material and synovial, pleural, CSF liquids, etc. A minimum of two and a maximum of three specimens per patient will be appraised in this study. Clinical specimens will not be collected out of the TB diagnostic investigation routine in the hospital.

Following the routine, the clinical samples will be forwarded to the mycobacteriology laboratories in the next working day. Only in the clinical samples of patients that have received randomization for the MGIT, should the laboratory personnel be informed that the MGIT must be performed.

To analyze the outcome of the study, the key information below, present in the medical handbooks or routine record cards of the TB Program, will be copied to the study’s own forms.

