**3.8. Definition of a TB Suspect Case, Active TB Case and Discordance Analysis**

**Pulmonary and /or pleural pulmonary form**

Every patient under pulmonary TB suspicion that presents respiratory signs/symptoms and with alterations in the chest X-ray will be classified in three groups;

a) Typical pattern of TB: infiltrated in upper third (LS or apical seg of LI), with or without cavity; bilateral miliar infiltration; unilateral pleural hemorrhage with upper lobe infiltration .

b) Intermediate pattern of TB: infiltrated in middle or lower third, with or without cavity in these areas; isolated pleural hemorrhage, infiltrated in upper thirds of undetermined activity; diffuse abnormalities (not miliar); mediastinal or hilar enlargement .

c) Atypical Pattern of active TB: multifocal hypotransparency images; alveolar hypotransparency images; calcified nodules.

“**Confirmed TB case"** will be defined as the patient with at least one positive culture for *M. tuberculosis* in L-J or MGIT960*.*

**“Probable TB case"** will be defined as the patient that presents negative results to culture with one or more of the following characteristics:

a) clinical answer to the treatment (defined as improvement to X-ray, b) decrease of the cough and 3% weight gain in relation to the beginning of the treatment) and absence of alternative diagnosis;

Patient not classified as confirmed case or probable TB will be considered "non- TB."

**Treatment failure:** patient that remains with positive bacteriological test (two samples in a 30 day interval) after 5 months of treatment, standardized by MH

High risk factors for resistant TB:

a) Relapsing TB (previous complete treatment for TB with apparent cure), b) Treatment failure (patient under treatment ≥ 4 months with positive bacilloscopy), c) Patient’s contact with multidrug resistant-TB.

3.9 **Main outcome**  The primary outcome was defined as the proportion of patients in each group whose initial prescription changed by the second month after randomization. The ‘change’ could be initiating or stopping TB treatment.

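### Section 3.5.1 has specimens cultured and susceptibility-tested by both MGIT and Löwenstein-Jensen methods regardless of arm, contradicting the one-method allocation in the synopsis and sections 3.5 and 3.6, so the randomised contrast is inconsistently defined

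*Protocol*

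**What the plan says.** Three places describe a one-method allocation.

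- Synopsis, Intervention: after randomisation, "TB suspects will be submitted to MGIT or culture in solid Löwenstein-Jensen medium (gold standard").
- Section 3.5: "clinical specimens from TB suspects will be submitted to MGIT or culture in Löwenstein Jensen solid medium (gold standard").
- Section 3.6 (Randomization): the physician opens the envelope and "inside it he/she will identify which is the diagnostic method that should be requested for the patient". The same section adds a laboratory rule: "Only in the clinical samples of patients that have received randomization for the MGIT" is the laboratory to be told to run MGIT.

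Section 3.5.1 describes something else. After processing, "they will be cultivated by the BACTEC MGIT 960 method and in Löwenstein-Jensen in Rio de Janeiro and in Vitoria". For included patients, "the sensitivity test will be carried out by the gold pattern tests and by BACTEC MGIT 960". Neither sentence mentions the allocated arm.

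Four other places bear on the point.

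- The closing paragraph of section 3.5.1 assigns one technician to process the daily specimens and inoculate them on LJ, again without reference to arm.
- Section 3.6.2 sends one sheet of each laboratory requisition, carrying the result, back to the clinic.
- In section 3.8 a confirmed case "will be defined as the patient with at least one positive culture" in either medium.
- Section 3.9 sets the primary outcome: the proportion whose initial prescription changed (TB treatment started or stopped) by month 2.

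**The concern.** In a trial of a diagnostic test, the intervention is the result that reaches the treating physician. The protocol should therefore fix which tests each arm receives. Here the methods section and the allocation rule disagree, and a laboratory that followed section 3.5.1 would run a different trial from one that followed section 3.6.

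Two things are at stake. If MGIT is also run for LJ-arm patients and reported in the usual way, those physicians act on the test under evaluation, and the difference in prescription changes shrinks. If instead the MGIT arm has LJ as well, a contrast survives, but it compares two cultures with one, and a gain could not be credited to MGIT alone. No analysis can restore a contrast that was lost in the laboratory.

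**Working it through.** **1. The texts side by side**

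| Reading | Text that supports it | Text against it |
|---|---|---|
| MGIT v LJ | Synopsis; section 3.5; envelope rule in 3.6 | Culture and susceptibility sentences of 3.5.1 |
| MGIT plus LJ v LJ | LJ inoculation of daily specimens (3.5.1) with MGIT only in its arm (3.6) | Synopsis and 3.5 (one or the other) |
| Both in everyone | Culture and susceptibility sentences of 3.5.1 | Synopsis; 3.5; 3.6 |

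Section 3.5.1 also sends positive cultures to the indirect proportions test, which it describes as starting from growth on solid medium. MGIT-arm isolates would thus need solid culture at some stage, and the protocol does not say how.

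**2. Could a non-allocated result arrive in time?** The Rationale gives 10 to 15 days for MGIT and 4 to 6 weeks of incubation for LJ. Month 2 is about 8 weeks, so either culture result can arrive before the primary outcome is fixed. Susceptibility by the proportions method is slower: 4 to 6 weeks of growth plus 28 days of incubation is about 8 to 10 weeks.

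**3. The plan's own figure.** Section 3.10 gives a 10-point difference, 80% power, the 5% level and at least 770 participants. It gives no control rate, sidedness or allocation ratio. I assume two-sided testing, 1:1 allocation, no dropout, and 40% v 50%:

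n per arm = (1.960 + 0.842)² × [0.40 × 0.60 + 0.50 × 0.50] / 0.10² = 7.849 × 0.49 / 0.01 = 384.6, so 385 per arm and 770 in all.

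The pooled-variance form gives 2 × 388 = 776. A control rate near 40-50% is thus compatible with 770, but the protocol does not state one.

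**4. Illustration of dilution.** Let a share f of LJ patients have an MGIT result released, and assume that they then respond as MGIT-arm patients do. With control rate p, the LJ arm has p₁ = p + 0.10f, the MGIT arm has p₂ = p + 0.10, and the difference is d = 0.10(1 − f). With n = 385 per arm and p̄ the mean of p₁ and p₂:

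power = Φ{ [d − 1.960 √(2p̄(1 − p̄)/n)] / √([p₁(1 − p₁) + p₂(1 − p₂)]/n) }

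For p = 40% and f = 25%: d = 0.075, p₁ = 0.425, p₂ = 0.50, p̄ = 0.4625. The numerator is 0.075 − 1.960 × 0.03594 = 0.00457 and the denominator is 0.03583. The ratio is 0.127, so power is 55%.

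| f (assumed) | Difference, points | Power, control rate 40% | Power, control rates 10-45% | Total N for 80% power, control rate 40% |
|---|---|---|---|---|
| 0 | 10 | 80% | 79-97% | 776 |
| 10% | 9 | 71% | 71-93% | 960 |
| 25% | 7.5 | 55% | 55-81% | 1,386 |
| 50% | 5 | 28% | 28-45% | 3,130 |
| 100% | 0 | 5% (false-positive rate) | 5% | none |

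**The case against.** The strongest reply is that the allocation is defined. The synopsis and section 3.5 state it, and section 3.6 gives an operational rule that directly excludes MGIT in the LJ arm. The culture sentence of 3.5.1 is visibly garbled: it names MGIT twice and mentions Vitoria, which is not in the site list of section 3.1. This stands in part. A reader might infer that the contrast is undefined, or that it is bound to vanish. The documents do not support that. It would vanish only if 3.5.1 overrode 3.6 and MGIT results of LJ-arm patients also reached physicians before month 2, and the protocol does not say that this happens. But the reply does not remove the contradiction, because 3.6 limits MGIT without saying that the MGIT arm goes without LJ, and the susceptibility sentence of 3.5.1 is not garbled.

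Other limits also stand.

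- The case definition that accepts either medium fits a one-method design too, so it proves nothing by itself. It matters only if some patients have both cultures.
- The technician paragraph describes division of labour. It leaves LJ in the MGIT arm possible but does not state it.
- Dual susceptibility testing bears mainly on the resistance outcomes, since the proportions result comes at or after month 2.
- A reader might take the Rationale's 80-85% culture sensitivity and compute the extra yield of a second culture. That range stands in a sentence about culture on solid LJ medium. The protocol gives no sensitivity for MGIT and nothing on the dependence between the two cultures, so no such figure is supported.
- MGIT added to routine LJ is a legitimate pragmatic question if it is declared. The synopsis speaks of comparison with routine culture methods.

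**Conclusion.** The point holds as a contradiction in the text. Section 3.5.1 cannot be followed together with the synopsis, section 3.5 and section 3.6, and the randomised contrast is inconsistently defined among three readings. Because the trial is open and results go back to the clinic by default, following 3.5.1 could erode the primary comparison.

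The size is illustrative only. Power would be about 55% or 28% instead of 80% at a 40% control rate if 25% or 50% of LJ patients had MGIT results released, and 55-81% or 28-45% over control rates of 10-45%. The control rate, the crossover shares, two-sided testing, 1:1 allocation and no dropout are all assumptions. If MGIT stays in its own arm, as 3.6 says, the planned sample size and power are unaffected. What then remains open is whether the comparison is MGIT v LJ or MGIT plus LJ v LJ.

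**What to change.** - Rewrite the culture and susceptibility sentences of section 3.5.1 to agree with the synopsis and sections 3.5 and 3.6. Restrict MGIT culture and MGIT susceptibility testing to the MGIT arm, as 3.6 already requires of MGIT.
- State whether the MGIT arm also receives LJ. If it does, name the comparison throughout as MGIT plus LJ v LJ. That choice is the sponsor's.
- For the between-arm comparisons of time to diagnosis, positive-culture proportion and confirmed TB, state which method's result counts in each arm.
- Reconcile the reporting text in section 3.6.2 with the allocation, so that it is clear how any non-allocated result would be handled. Whether a result goes to the physician is a matter of clinical management, and nothing here asks that any result be withheld.
- Reconcile the mention of Vitoria with the site list in section 3.1.

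The cost is protocol wording and one laboratory instruction. The sample size does not change.
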